### Control intervention

The participants in the control condition will receive CAU, as this provides an appropriate comparison with routine clinical practice and will address the issue of whether ACT plus CAU is more effective than CAU alone. CAU components will be actively recorded as part of the trial but are likely to include allocation of a keyworker when one becomes available, with subsequent contact as required. All contact is usually conducted at the service via an appointment based system. Participants will receive a full assessment of alcohol, social and physical health needs, and a risk assessment. CAU focuses primarily on alcohol use and promoting abstinence and relapse prevention. It includes access to medical detoxification, psychological interventions focused on drinking behaviour and available aftercare as required. CAU may also include input from specialists in addictions psychiatry, clinical psychology and social work where available. Patients are most often signposted to other relevant agencies when these services are not directly provided by the addiction treatment service. Aftercare will typically be provided outside the community addiction services. The majority of patients are discharged to primary care within 12 weeks of being allocated a keyworker unless there are significant risks identified. Failure to attend appointments also results in discharge from the service. To establish the variability of CAU for a full-scale trial, interviews will be undertaken with team leaders at each study site and an additional four national sites examining care pathways.

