#### Follow up assessments

Six months and 12 months after randomisation, all participants will be followed up. A research worker, blind to treatment allocation, will arrange a convenient time to meet with the participant in order to complete the following measures:

(i) Changes in socio-demographic details - change in relationship status, living arrangements, and living arrangements of children

(ii) Timeline Followback form 90I

(iii) Drug use in previous 90 days - Timeline Followback

(iv) Alcohol Problems Questionnaire

(v) Severity of Alcohol Dependence Questionnaire

(vi) EQ-5D

(vii) SF-12

(viii) Readiness to Change

(ix) Important People and Activities Inventory

(x) York Service Use Questionnaire

(xi) Therapeutic relationship - STAR [37]

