### Sample size and power calculation

As this study is the first to examine the effect size of ACT in alcohol dependence, there is no specific study on which to base the power calculation. In terms of alcohol consumption a proportional difference between the groups of 30% would be considered a clinically important difference. This equates to an effect size difference of 0.70 similar to the effect sizes found in Patterson et al study [38] and the Cochrane meta-analysis of ACT [19]. As a pilot study we have employed an alpha of 0.2 and power of 80%, a sample of 35 in each group followed-up at 12 months would allow us to detect an effect size of the order of 0.5, a more conservative estimate of effect than seen in similar studies. Allowing a loss to follow-up of 25% would suggest we require 45 in each group, a total of 90 participants. This number would allow us to estimate the potential effect, within 80% confidence intervals in order to enable more formal sample size calculations for a definitive study.

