### Statistical analysis

The main hypothesis, stated as a null hypothesis, is that CAU augmented with ACT is no more effective than CAU in reducing alcohol consumption 12 months after randomisation. The primary outcome measures will be alcohol consumption: mean drinks per drinking day and percentage of days abstinent at 12 months measured using the Timeline Followback interview. The primary analysis will be intention-to-treat in which participants will be analysed as part of their allocated group irrespective of the treatment received; this provides the most rigorous estimate of effectiveness. The primary outcome measure will be analysed using an analysis of covariance approach adjusting for known confounding variables such as baseline mean drinks per drinking day, age and gender. If the assumptions underlying ANCOVA are not met transformations will be undertaken and if transformations are not viable alternative non-parametric approaches will be used. In order to explore the impact of missing data on the primary outcome measure we will employ multiple imputation techniques and conduct sensitivity analyses to measure any effect of missing data on reported outcomes.

Continuous secondary measures will be analysed in a similar manner. Categorical variables will be analysed using chi-squared statistics and binary outcomes analysed using logistic regression controlling for known confounding variables. Estimates and the 80% confidence intervals will be presented. In addition intra-class correlation coefficients relating to therapists will be calculated and estimates of recruitment, engagement in treatment, retention will be assessed to inform any future study.

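### The primary 12-month ANCOVA appears to be an observed-case analysis that makes no use of the 6-month drinking data, so loss tied to 6-month drinking differently by arm could bias the effect estimate

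*Protocol article*

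**What the plan says.** All of this is in the Protocol article.

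- **Statistical analysis.** The primary outcomes are mean drinks per drinking day and percentage of days abstinent at 12 months. They are analysed by allocated group with ANCOVA, adjusted for an open list of covariates that names baseline drinks per drinking day, age and gender. No 6-month value is named. On missing data: "In order to explore the impact of missing data on the primary outcome measure we will employ multiple imputation techniques and conduct sensitivity analyses". The variables in the imputation model are not given.
- **Follow up assessments.** "Six months and 12 months after randomisation, all participants will be followed up", by a blinded research worker. Timeline Followback is on the list for both visits.
- **Sample size and power calculation.** "a sample of 35 in each group followed-up at 12 months would allow us to detect an effect size of the order of 0.5", and then "Allowing a loss to follow-up of 25% would suggest we require 45 in each group, a total of 90 participants".
- **Control intervention.** On usual care (CAU): "The majority of patients are discharged to primary care within 12 weeks" of getting a keyworker, and non-attendance also leads to discharge. Under **Intervention**, ACT calls for at least weekly contact for a year and persistent attempts to re-engage.

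**The concern.** The article sets an order: ANCOVA gives the result, and imputation examines how far missing data matter. An ANCOVA needs an observed 12-month value, and no other handling of missing values is attached to the primary model. The power statement also counts only people seen at 12 months. Read together, these make the primary estimate look like an observed-case one.

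Such an estimate is valid if, given arm and the covariates, being seen at 12 months is unrelated to the 12-month outcome. Someone drinking heavily at 6 months may be harder to find at 12 months. If that link is stronger in one arm than the other, the completers in the two arms are no longer comparable, and adjusting for baseline does not fully repair it. The 6-month interview records the relevant information, but the named primary model does not use it.

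The trial exists to supply an effect size for a definitive study. Required sample size varies as 1/d², so planning on 0.45 instead of 0.50 multiplies it by (0.50/0.45)² = 1.23, and planning on 0.38 by (0.50/0.38)² = 1.73.

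**Working it through.** **1. The plan's own figures.** Inputs from Sample size and power calculation: alpha 0.2, power 80%, d = 0.5, 25% loss, 45 recruited per group.

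- Two-sided n per group = 2(z₀.₉₀ + z₀.₈₀)²/d² = 2(1.2816 + 0.8416)²/0.25 = 36.06, so 37, against 35 stated. Power at 35 per group is 79.1%. The figure is reproduced to within 2 per group.
- 45 × 0.75 = 33.75, so about 34 per group would enter an observed-case ANCOVA.
- Half-width of the 80% confidence interval, unadjusted: 1.2816 × √(2/34) = 0.31 SD.

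**2. Assumptions for the bias check.** The document gives no correlations and no dropout mechanism, so these are assumed: normal outcomes with SD 1, true effect 0.50 SD, 25% total loss per arm, and a log-odds slope for loss of 1 per SD of drinking. Two estimators of the 12-month contrast are compared in large simulated samples:

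- (A) ANCOVA on observed 12-month cases, adjusted for baseline;
- (B) the same contrast after predicting missing 12-month values from baseline and the 6-month value, a stand-in for multiple imputation or a repeated-measures likelihood model.

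**3. All loss after 6 months.** Baseline-to-follow-up correlation 0.3 to 0.5, 6-to-12-month correlation 0.5 to 0.7.

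| Loss depends on | A | B |
|---|---|---|
| baseline drinking only | 0.50–0.51 | 0.50–0.51 |
| 6-month drinking, same way and rate in both arms | 0.50–0.51 | 0.50–0.51 |
| 6-month drinking, CAU only | 0.38–0.45 | 0.50–0.51 |
| 6-month drinking, opposite directions by arm | 0.23–0.39 | 0.50 |

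In the CAU-only row the bias is 0.50 − 0.45 = 0.05 to 0.50 − 0.38 = 0.12.

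**4. Part of the loss before 6 months.** Total retention 75% per arm; informative loss in CAU only. Correlations are baseline-to-follow-up / 6-to-12-month.

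| Where the informative loss falls | A, B at 0.5/0.7 | A, B at 0.4/0.5 |
|---|---|---|
| after 6 months, driven by 6-month drinking (10% random loss earlier) | 0.43, 0.50 | 0.45, 0.50 |
| before the 6-month visit (20% lost), driven by drinking then | 0.42, 0.42 | 0.44, 0.44 |
| after 6 months, driven by 12-month drinking | 0.39, 0.43 | 0.38, 0.40 |

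**5. At the trial's size.** A Monte Carlo run of 6000 trials with 45 per arm, correlations 0.5/0.7 and 10% random early loss gave a mean for A of 0.41 when retention was 73% v 75%, and 0.38 when it was 66% v 83%. With correlations 0.4/0.5 the bias was 0.07. With the same dependence on drinking in both arms it was 0.02. The variance of B ranged from 1% higher to 6% lower than that of A, so using the 6-month data cost essentially no precision.

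**The case against.** **The article never states a completers' restriction.** That is correct: it is inferred from the model, the role given to imputation and the power statement. The order of the analyses, however, is stated, and imputation can only explore the impact of missing data against an analysis done without it.

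**Missing data are already addressed.** Imputation and sensitivity analyses are promised, and the content of an imputation model belongs in the SAP, which is not shown. So the 6-month data cannot be said to be ignored throughout: the planned imputation may use them. What remains is which estimate leads when the two disagree, and the article gives that place to the ANCOVA.

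**Discharge from the service is not loss from the trial.** A reader might infer from the CAU discharge practice that drinking-related loss will be greater in that arm and that ACT will therefore look worse than it is. The document does not support this. Research workers arrange both interviews with all participants, independently of service contact. Differential loss is plausible but assumed, and so is its direction.

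**The remedy works only for some mechanisms.** This stands. Early discharge would, if anything, act before 6 months, where using the 6-month outcome gains nothing. It would be wrong to infer that the change removes the bias generally.

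**The size is modest for an exploratory trial.** A bias of 0.05 to 0.12 SD compares with an 80% interval half-width of 0.31 SD. That bears on priority. It does not remove the point, because the interval conveys sampling error and not bias.

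**The outcomes may not be normal.** The plan allows for transformation or non-parametric methods, and the simulations used normal data. The fix has to accommodate this.

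**Conclusion.** The point holds as a low-cost improvement, not as a demonstrated error. The primary ANCOVA appears to be an observed-case analysis without the 6-month outcome, and imputation is placed beside it rather than behind the headline estimate. Loss after 6 months that depends on 6-month drinking in one arm only would bias a true 0.50 SD effect by about 0.05 to 0.12 SD under the assumed correlations, slope and 25% loss. Dependence in opposite directions by arm would do more harm.

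A 25% loss does not by itself produce bias. There is no material bias if loss is random, depends on baseline only, or relates equally to drinking in both arms at similar rates. In none of the scenarios examined was the estimate using 6-month data materially further from the true effect than the observed-case ANCOVA.

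**What to change.** State that the primary estimate is the 12-month contrast from a method that uses the 6-month Timeline Followback outcome. Either route will do:

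1. a repeated-measures likelihood model of the 6- and 12-month outcomes, with arm, visit, arm by visit, the outcome's own baseline value, the stratification factors (SADQ category and site) and unstructured covariance; or
2. multiple imputation done separately by arm, including the 6-month outcome, followed by the planned ANCOVA.

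Apply the chosen method on the transformed scale wherever the plan's provision for transformation is triggered. The imputation route is easier for skewed drinks per drinking day and a bounded percentage of days abstinent. Keep the observed-case ANCOVA as a sensitivity analysis. Specify that the planned sensitivity analyses include arm-specific departures from missing at random, because the change does nothing for informative loss before 6 months and only partly corrects loss driven by 12-month drinking.

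Cost: no new data, a little more modelling (a few covariance parameters, or an imputation model to specify), and an explicit missing-at-random assumption, which is weaker than the one the observed-case ANCOVA needs.

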### Intervention

#### Assertive community treatment intervention

ACT was originally developed for patients with psychotic disorders and has become an established model of care for this population in the US and UK. Since this intervention has never been used for people with primary alcohol dependence, the research team will implement an ACT model taking into account the original model and recent research identifying effective elements in UK studies. A treatment manual will be developed by the research team together with experts in the provision of ACT and incorporating existing research evidence.

The ACT intervention will comprise the following:

(i) Maximum caseload of 15 ACT patients per ACT practitioner

(ii) Input from a multidisciplinary team (including psychiatrists, substance misuse specialists)

(iii) Regular contact (minimum of once a week; 50% of contacts outside of the service settings, either in the patients' home or neighbourhood; short frequent contacts rather than long complex contacts will be encouraged).

(iv) Assertive engagement - persistent and repeated attempts to contact, emphasis on maintaining contact and building relationships

(iii) Focus on both health and social care needs - including accommodation, leisure, occupation, and physical and mental health

(iv) Flexibility - practitioners should work flexibly with patients' goals even when these are peripheral to the addiction.

(v) Openness - practitioners are explicit about their goals both in care planning and in visits.

(viii) Going out of your way - stepping outside of professional roles and going the extra mile for patients.

(ix) Extended care - provided for a prolonged period of 1 year.

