#### Training

The training will comprise a three day workshop and a one day clinical placement. The workshop will provide specialist addiction clinicians with information about ACT, its' history, implementation in mental health and the ACTAD trial. Following the workshops each practitioner will attend a one day placement with a mental health assertive outreach team. They will shadow a member of staff including attending community and home visits with patients and have the opportunity to ask questions regarding the day to day practice of providing ACT. A final training day will focus on ACT practice in addictions. A minimum of three members of staff at each site will receive the training.

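### Neither the sample size nor the described ANCOVA allows for clustering of ACT patients within a few practitioners; if the practitioner ICC is positive, the 80% intervals are too narrow and the stated power too high

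*Protocol article*

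**What the plan says.** - **Delivery.** The intervention section sets a "Maximum caseload of 15 ACT patients per ACT practitioner", with at least weekly contact over one year. The Training section adds: "A minimum of three members of staff at each site will receive the training". The number of staff who will actually deliver ACT is not given. The Overview describes two centres, while the Process evaluation section refers to three sites.
- **Sample size.** "As a pilot study we have employed an alpha of 0.2 and power of 80" per cent, and "a sample of 35 in each group followed-up at 12 months would allow us to detect an effect size of the order of 0.5". The only inflation is for 25% loss to follow-up, giving 45 per group and 90 in total. No ICC or design effect appears.
- **Analysis.** The primary outcomes are analysed by intention-to-treat ANCOVA on patients. Baseline drinking, age and gender are given as example covariates, and estimates come with 80% intervals. The same section says that "intra-class correlation coefficients relating to therapists will be calculated", next to recruitment, engagement and retention estimates, all meant for planning a later trial.
- **Control arm.** CAU is expected to include a keyworker once one is free. Most patients are discharged within 12 weeks of that allocation.

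**The concern.** Patients who share an ACT practitioner may have correlated outcomes. ACT depends on the worker's persistence, flexibility and relationship with the patient, and the Process evaluation section itself sets out to look at differences between practitioners. The plan therefore recognises the clustering, but gives it no role in this trial's own standard errors.

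That matters because the interval is a main product of the trial. The sample size section justifies 90 participants partly by the 80% interval they will give, which is to feed the definitive trial's sample size. An interval that ignores a positive ICC presents the effect as better known than it is. Using the ICC only in the next trial's design effect does not correct the effect interval that enters the same calculation.

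**Working it through.** **Inputs from the protocol:** alpha 0.2, power 80%, effect size 0.5 (SD = 1), 35 analysed per group, 25% loss, 45 randomised per group, maximum caseload 15, at least three trained staff per site, two or three sites.

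**Assumed, because the protocol gives no value:** ICC of 0.02, 0.05 or 0.10; k = 3, 6 or 9 practitioners; clustering in the ACT arm only.

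**1. Reproduce the plan's figure.** Two-sided, independent patients:
- n per group = 2 × (1.2816 + 0.8416)² / 0.5² = 36.1, so 37, against 35 stated.
- Power at 35 = Φ(0.5/√(2/35) − 1.2816) = Φ(2.092 − 1.282) = 79.1%.
- Detectable effect at 35 = 2.1232 × √(2/35) = 0.508, which fits the stated order of 0.5.
- A one-sided test would need only 23 per group and does not fit.

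The stated figure thus reproduces with a design effect of 1, leaving no margin for clustering.

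**2. Number of practitioners.** 45 / 15 = 3 at the caseload limit. Three trained staff at each of two or three sites gives 6 or 9.

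**3. Add clustering in the ACT arm.**
- m = 35/k and DE = 1 + (m − 1) × ICC
- SE = √(DE/35 + 1/35)
- Ratio of true to reported SE = √((DE + 1)/2)
- Power of a test that uses the correct SE = Φ(0.5/SE − 1.2816)
- Coverage of the unadjusted 80% interval = 2Φ(1.2816/ratio) − 1

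Example, k = 6 and ICC 0.05: m = 5.83; DE = 1 + 4.83 × 0.05 = 1.242; SE = √(2.242/35) = 0.253; ratio = √(2.242/2) = 1.059; power = Φ(1.976 − 1.282) = 75.6%; coverage = 2Φ(1.210) − 1 = 77.4%.

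| Practitioners | ICC | DE (ACT) | SE ratio | Cluster-adjusted power | Coverage of unadjusted 80% interval |
|---|---|---|---|---|---|
| any | 0 | 1.000 | 1.000 | 79.1% | 80.0% |
| 9 | 0.02 | 1.058 | 1.014 | 78.2% | 79.4% |
| 9 | 0.05 | 1.144 | 1.035 | 77.0% | 78.4% |
| 9 | 0.10 | 1.289 | 1.070 | 75.0% | 76.9% |
| 6 | 0.02 | 1.097 | 1.024 | 77.7% | 78.9% |
| 6 | 0.05 | 1.242 | 1.059 | 75.6% | 77.4% |
| 6 | 0.10 | 1.483 | 1.114 | 72.4% | 75.0% |
| 3 | 0.02 | 1.213 | 1.052 | 76.0% | 77.7% |
| 3 | 0.05 | 1.533 | 1.125 | 71.8% | 74.5% |
| 3 | 0.10 | 2.067 | 1.238 | 65.8% | 69.9% |

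The last two columns describe different procedures. Power is for a test that allows for clustering; coverage is for the interval that does not. The true type I error of the unadjusted test is 100% minus the coverage.

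**4. Variations.**
- If CAU patients cluster by keyworker to the same degree, SE = √(2 × DE/35). At ICC 0.05, power is 72.4% with 6 keyworkers per arm and 65.8% with 3.
- At the clinically important effect size of 0.70, power stays between 86% and 95% over the whole range with clustering in the ACT arm only.
- These large-sample formulas ignore the few degrees of freedom that 3 to 9 practitioners provide. Baseline adjustment may recover some power, but the baseline correlation is not given.

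**The case against.** **The article is condensed.** The covariate list is open-ended, and an analysis plan that is not shown may contain a practitioner term. A reader might infer that the plan commits to treating patients as independent in the analysis; the text does not say so. This limits the analysis half of the point to what is described. It does not touch the sample size, which is fixed in the text without a design effect.

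**The consequence is conditional.** A reader might also conclude that the intervals are too narrow as a matter of fact. The documents do not support that, since they give neither an ICC nor a practitioner count. Three practitioners would require every one to be at the caseload limit, and with 6 to 9 and a small ICC little changes. This stands.

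**CAU may cluster too.** It would be wrong to assume that only ACT patients share staff. Shorter contact in CAU weakens the nesting but does not remove it. This also stands; it makes the power loss larger, and a random effect confined to the ACT arm would then be misspecified.

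**The remedy has limits.** In a simulation of a balanced partially nested model with Satterthwaite degrees of freedom at ICC 0.05, the practitioner variance was estimated as zero in about 42% (6 practitioners) to 45% (3) of trials. Intervals were on average about 12% to 30% wider than the unadjusted ones, with coverage of about 82% to 83%. That is a fair reason not to make this model the main analysis.

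**The trial is exploratory.** A lenient alpha and an approximate target effect are declared openly, and estimating the ICC for later use is a legitimate aim. That lowers the stakes of the test, but not of the interval, which is meant to be handed on.

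**Conclusion.** The point holds in conditional form. Therapist clustering is named in the plan but kept for a future trial, and neither the sample size nor the described primary analysis allows for it. Within the assumed range, the loss runs from about one point of power and coverage (ICC 0.02, 6 to 9 practitioners) to about 13 points of power and 10 of coverage (ICC 0.10, 3 practitioners). A middle case of 6 practitioners and ICC 0.05 costs about 3.5 points of power and 2.6 of coverage. These sizes rest on the assumed ICCs, equal caseloads, 35 analysed per arm and no clustering in CAU. The point does not undermine the trial's design; it concerns how honestly its interval is reported and passed on.

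**What to change.** 1. Keep the ANCOVA as planned. Beside it, pre-specify for each primary outcome a practitioner-adjusted 80% interval from a partially nested mixed model with small-sample degrees of freedom (Satterthwaite or Kenward-Roger). Include keyworker clustering in CAU where the contact log shows it.
2. Because the ICC will be poorly estimated, also give the interval at fixed ICCs of 0.02, 0.05 and 0.10.
3. Use the adjusted interval in the definitive trial's sample size calculation.
4. State that the power in the sample size section holds only for independent patients, and give the range tabulated above.
5. State how many practitioners will deliver ACT, and reconcile the two-centre and three-site descriptions, since they bear on that number.

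If an existing analysis plan already has a practitioner term, only items 3 to 5 and the fixed-ICC intervals remain. The cost is a few lines of code and no change to recruitment or care: the contact log already records the staff member at each contact in both arms. The price is wider intervals and an imprecise practitioner variance, often estimated as zero, which is why the adjusted interval sits beside the planned analysis rather than replacing it.
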